### Primary outcomes

1. Difference in ASPECT scores provided by e-ASPECTS versus expert human readers.2. Diagnostic accuracy of e-ASPECTS versus expert human readers for identifying the cause of stroke symptoms (i.e. ischaemia, haemorrhage, other).

### Secondary outcomes

1. Proportion of scans successfully versus unsuccessfully processed by e-ASPECTS (i.e. where ASPECTS results are provided or not provided), factors associated with e-ASPECTS processing success and result accuracy.2. Proportion of ICA-MCA occlusion versus normal ICA-MCA axis correctly identified by e-CTA, accuracy of e-CTA for detecting any intracranial obstruction, difference in CTA collateral scores provided by e-CTA versus expert human readers.3. Repeatability of e-ASPECTS and e-CTA results on a subset of scans presented twice.

### Tertiary outcomes

1. Difference in haemorrhage size and location results provided by e-ASPECTS versus expert human readers.2. Potential clinical impact of e-ASPECTS and e-CTA on routine acute stroke care, whether: a. knowledge of ASPECTS conveyed using e-ASPECTS visual overlay on imaging influences diagnostic confidence or alters treatment decisions,b. use of e-ASPECTS/e-CTA alter the time required for scan interpretation, andc. e-ASPECTS or e-CTA results are associated with outcome after ischaemic stroke.

### Dissemination of results

We will include all primary and secondary outcomes in the primary RITeS publication.

Tertiary outcomes require additional expert-human data to be collected and will therefore be reported separately, subsequent to the primary RITeS publication.

## Statistical analysis

### Analysis principles and general considerations

Primary and where appropriate, secondary outcome testing will be conducted on an ‘intention-to-analyse’ basis irrespective of whether scan processing was successful or not◦ Processing will be considered successful when an ASPECTS (0-10) or CTA result (occlusion/no-occlusion or scalar collateral score) is provided, or when arterial hyperattenuation or haemorrhage is detected.◦ We will record all software failures whether these occur at the scan upload, scan processing, or results output stage.We will use mean (standard deviation, SD) or median (inter-quartile range, IQR) to represent the distribution of parametric and non-parametric data, respectively. We will use n (%) for categorical data.Where possible, we will use diagnostic accuracy statistics as the principal method in RITeS for comparing software and expert human results. With expert human results as the reference standard, we will calculate true/false positive/negative cases (TP, FP, TN, FN, respectively) and derive sensitivity (TP/TP+FN), specificity (TN/TN+FP), positive predictive (TP/TP+FP), negative predictive (TN/TN+FN), and accuracy (TP+TN/TP+TN+FP+FN) percentages as standard. We will calculate 95% confidence intervals for each using the Wilson score method^37^. ◦ For all diagnostic accuracy testing we will include random-effects meta-analysis modelling of individual patient data (i.e. a one-step meta-analysis) to provide overall estimates of sensitivity and specificity, to assess variation within and between the 10 RITeS studies, and to account for clustering of individual study results^38^,^39^.◦ For each of the 10 RITeS studies, we will use the PROBAST method for assessing risk of bias in diagnostic modelling^40^. For all comparisons of software and expert human results, we will review side of affected brain data to ensure ASPECTS and CTA results are correctly matched for each cerebral hemisphere, i.e. matched results require same score and side. We will separately test whether knowledge of affected side impacts the accuracy of e-ASPECTS results, see secondary outcomes below.Bland-Altman plots^41^ will be used to visually compare software and expert human results, comparing mean score differences to assess the magnitude, direction and distribution of error and will use ± 1.96 SD to determine the range of agreement^42^. For software and expert human results to be considered equivalent, we will set maximum clinically acceptable limits of agreement for individual scores, specified in the relevant sections below.Krippendorff’s Alpha^43^ (K-alpha) will be used to assess reader (human-human and human-software, as necessary) agreement. K-alpha is generally more robust than kappa in this context since it can handle categorical and ordinal data, works where there is missing data, adjusts for small sample sizes, and includes multiple observers simultaneously^43^,^44^. K-alpha results are interpreted similarly to kappa with scores ranging from -1 (perfect disagreement) to +1 (perfect agreement). We will therefore also use the Landis and Koch method for interpreting K-alpha results (as commonly used for kappa): 0.00–0.20=slight agreement, 0.21–0.40=fair agreement, 0.41–0.60=moderate agreement, 0.61–0.80=substantial agreement and 0.81–1.00=almost perfect agreement^45^.Other specific statistical tests are listed in the following sections.For multivariable testing, we will check for multicollinearity between included variables by identifying variance inflation factors (VIF) >5. Where multicollinearity is detected, we will run separate (but otherwise equivalent) multivariable regression models for each of the internally correlated variables.We will not impute but will report missing data (proportions of data missing for each variable and observations not included in analyses).We will use SPSS, IBM Corporation (Armonk, USA) and/or R (https://www.r-project.org/) statistical software for all analyses. We will preferentially report 95% confidence intervals, but where appropriate, we will report p-values.

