### Inclusion and exclusion criteria

We will derive separate but overlapping samples for e-ASPECTS and e-CTA testing from all baseline scan data available to RITeS. We will produce a STARD-type (Standards for Reporting Diagnostic Accuracy Studies) flow chart^24^ to show reasons for inclusion/exclusion of cases and successful/non-successful scan assessment by human-readers and software for all patients available to RITeS.

**
*Sample for e-ASPECTS evaluation.*
** There are no precise data for the true case-mix of patients initially assessed for presumed stroke, and for whom hospital admission staff may decide to use e-ASPECTS and e-CTA software to assess treatment eligibility. Pooled data from the major thrombolysis and thrombectomy RCTs will be similar to the case-mix considered for these treatments but may include patients with more severe stroke than those seen in routine practice and will not include patients who present late^4^,^25^. Conversely, patients with haemorrhagic stroke are most likely to be severely affected by stroke symptoms^26^, and a proportion may be too sick to be appropriately represented in trials. The Sentinel Stroke National Audit Programme (SSNAP) provides routinely collected UK data for all patients ultimately diagnosed with stroke in England, Wales and Northern Ireland and includes many patients with minor symptoms or delayed/uncertain time of presentation who would not routinely be considered for thrombolysis or thrombectomy^27^. Importantly, all of these data sources only include patients after excluding structural stroke mimics. RIGHT-2 recruited patients at first contact with ambulance staff in the community and reported 26% stroke mimics^17^. A prospective single-centre study of patients with suspected stroke following stroke expert review after arrival at hospital found a similar proportion of mimics^28^. Additionally, in up to 7% of patients with stroke, it is only possible to obtain imaging of poor quality due to patient movement, beam hardening artefacts or variable patient orientation in the scanner, all of which may influence the performance of e-ASPECTS and e-CTA software^3^,^11^. Finally, the sensitivity and specificity of diagnostic tests may vary with prevalence^29^. 

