We will classify e-ASPECTS and expert-human scores into three groups to assess diagnostic accuracy at the following clinically relevant cut-points, and present a summary (receiver-operating characteristic) ROC curve: 1) ASPECTS 10 (normal) versus ASPECTS 0-9 (abnormal)2) ASPECTS 0-7 versus 8-10^2^.3) ASPECTS 0-5 versus ASPECTS 6-10^4^.

To compare with previous work, we will use Matthews correlation coefficient (MCC), and test non-inferiority between e-ASPECTS and expert-human scores^5^,^35^. We will calculate MCC as (TPxTN)-(FPxFN)/√(TP+FP)(TP+FN)(TN+FP)(TN+FN)^46^. We will set our non-inferiority margin at 5%. Thus using the two one-sided test (TOST) procedure, we will establish non-inferiority, using the following formula: at the α=5% significance level, if the lower limit of a (1-2α) × 100% (i.e. 90%) confidence interval for the difference (e-ASPECTS minus expert-human results) is above -5%. The confidence interval is set at (1-2α) rather than the usual (1-α) because the method is equivalent to performing two one-sided tests^47^,^48^.

**
*2. Accuracy of e-ASPECTS versus expert human readers for identifying cause of stroke symptoms.*
** We will compare the diagnostic accuracy of e-ASPECTS software and expert human readers (at baseline, blind to all other clinical data including further imaging) for three groups against the reference standard, human-expert opinion using all available follow-up data including further imaging: 1) Identifying features of ischaemic stroke (including ischaemic lesions in any brain location and/or intracranial hyperattenuating arteries)2) Identifying haemorrhage, and3) Identifying any structural causes of stroke symptoms on baseline imaging (including mimics).

In addition, to aid clinical understanding and real-world applicability, we will summarise all primary outcome results using normalised frequencies. Thus we will present results as proportions of 1000 individual patients, i.e. a test sensitivity of 90% would be presented as: the test will detect disease in 900 of 1000 patients with the disease, but 100 patients with the disease will be missed by the test^49^.

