## Figures and Tables

**Table 1. T1:** Clinical stroke trials with baseline CT scans available for inclusion in RITeS.

Stroke Trial	Number patients	Baseline CT Assessment	Stroke Type	Trial Type	Other Scans	Follow-up Data
ATTEST	104	ASPECTS	Isch	RCT – IV alteplase or tenecteplase	CT at 24–48 hrs	2 & 90 days
EuroHyp	98	As per IST-3, excluding CTA.	Isch	RCT – systemic cooling to 34-5°C for 24 hours or control	CT/MRI at day 5	0–7 & 90 days
IST-3	3035	Ischaemia extent & location, ASPECTS, swelling, atrophy, leukoaraiosis, old stroke lesions, arterial patency & collateral scores on CTA, scan quality 3.	Isch	RCT – IV alteplase or control	Baseline CTA (in ~270) CT/MRI at 24–48 hrs	7 days & 6- months
LINCHPIN	947 *	Location & size of intracerebral haemorrhage	Haem	Observational cohort study	MRI at 3 months	Post-mortem
PISTE	65	As per IST-3.	Isch	RCT – IV alteplase and thrombectomy or IV alteplase alone	Baseline CTA CT/MRI at 22–36 hrs	2 & 90 days
POSH	113	Ischaemia volume on CT, ASPECTS, arterial patency on CTA	Isch	Observational study	CT at 24–48 hrs	
PRACTISE	271	As per IST-3.	Isch	RCT – Multimodal CT imaging (CT + CTA + CTP) or CT alone	Baseline CTA (in 50%) CT/MRI at 24 hrs	1, 7 & 90 days
RESTART	537	Location & size of haemorrhage, atrophy, leukoaraiosis, old stroke lesions, scan quality	Haem	RCT – restart or avoid antiplatelets after haem stroke	MRI pre- randomization (in 550)	1–3 years
RIGHT-2	1149	As per IST-3.	Isch	RCT – ultra-early transdermal GTN or control	CT at 24–48 hrs	4 & 90 days, 1 year
SITS Open	293	ASPECTS, swelling, arterial patency on CTA	Isch	Controlled study -thrombectomy vs control	Baseline CTA (in ~5%) CT/MRI at 22–36 hrs	1, 7 & 90 days

* Ongoing at time of data collection.

**Table 2. T2:** Planned assessment of demographic and clinical data for non-stroke mimic cases within the RITeS dataset, and comparison with other datasets.

Clinical Feature		RITeS dataset	SSNAP dataset	STTC dataset	HERMES dataset	LATCH dataset
Total patient number			87,635	6,756	1,764	137
Female sex			48%	45%	47%	55%
Age, years			77 (66-85)	71 (13)	67 (57-76)	79 (67-83)
Aetiology	Ischaemia		87%	100%	100%	-
	Haemorrhage		12%	-	-	100%
NIH Stroke Scale			5 (2-11)	12 (7)	17 (13-21)	-
Glasgow Coma Scale			-	-	-	13 (9-15)
Time from stroke onset, hours			4 (2-11)	4 (1.2)	3 (2-4)	-

Note: Data are percentage, median (inter-quartile range), or mean (standard deviation) as appropriate.

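### For ischaemia and haemorrhage detection (primary outcome 2), variation between ten studies cannot be assessed as worded, because cases and non-cases come largely from different studies

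*SAP article*

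**What the plan says.** The SAP article, under Analysis principles and general considerations, sets one rule without exception: "For all diagnostic accuracy testing we will include random-effects meta-analysis modelling of individual patient data (i.e. a one-step meta-analysis". The model is meant "to provide overall estimates of sensitivity and specificity, to assess variation within and between the 10 RITeS studies" and to allow for clustering by study.

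Primary outcome 2 is accuracy for "identifying the cause of stroke symptoms (i.e. ischaemia, haemorrhage, other". The analysis section lists three targets. The first is "Identifying features of ischaemic stroke (including ischaemic lesions in any brain location and/or intracranial hyperattenuating arteries", the second is haemorrhage, and the third is any structural cause. The reference standard is "human-expert opinion using all available follow-up data including further imaging".

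Table 1 gives every study a single stroke type. LINCHPIN is haemorrhagic, with its baseline CT assessment given as "Location & size of intracerebral haemorrhage". RESTART is also haemorrhagic, described as "RCT – restart or avoid antiplatelets after haem stroke". The other eight are typed ischaemic.

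Two places mention some mixing within studies. Under Inclusion and exclusion criteria, "RIGHT-2 recruited patients at first contact with ambulance staff in the community" and reported 26% mimics. The tertiary haemorrhage analysis refers to bleeds classed as mimics in the ischaemic trials. The SAP does not say which studies feed which estimate, or how a study with only one disease status is handled.

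**The concern.** Sensitivity is estimated only from patients who have the target condition, and specificity only from patients who do not. A study with one status informs only one of the two. Where status follows study type, the number of studies behind each measure falls well below ten, and for one of the two measures it can fall to two or three.

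Two things are then at stake for a primary outcome. First, a between-study SD from two or three studies says almost nothing, and a Wald interval built on it is too short. Second, sensitivity and specificity for the same target come largely from different studies. A difference between the haemorrhage cohorts and the ischaemic trials then cannot be separated from a difference between cases and non-cases.

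**Working it through.** **1. Inputs (Table 1).**
- Ischaemic type: 104 + 98 + 3035 + 65 + 113 + 271 + 1149 + 293 = 5128.
- Haemorrhagic type: LINCHPIN 947 + RESTART 537 = 1484.
- Total: 5128 + 1484 = 6612, which agrees with the SAP's figure of over 6600. The haemorrhagic share is 1484/6612 = 22.4%.

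These are counts before representative sampling, which can only remove cases.

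**2. Studies able to contribute, by stroke type.**

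| Target | Sensitivity | Specificity |
|---|---|---|
| Haemorrhage | 2 studies, plus bleeds in ischaemic-type studies (count not given) | up to 8 studies |
| Ischaemia, judged by cause | up to 8 studies | 2 studies, plus mimics (count not given) |

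Neither target has ten studies behind both measures. The best-placed extra contributor is RIGHT-2. If all its patients are accessible and all reported mimics count, it supplies at most 0.26 × 1149 ≈ 299 ischaemia-negative mimics. This is an assumed ceiling: the SAP expects structural mimics overall to be far below 26%, and it gives no count of bleeds in RIGHT-2.

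**3. What k studies can say.** With k studies (df = k − 1), a mean takes the multiplier t(0.975, df). The 95% limits for a between-study SD are its estimate times √(df/χ²(0.975, df)) and √(df/χ²(0.025, df)). These formulae ignore sampling error within studies.

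| k | t multiplier | SD limits, × estimate |
|---|---|---|
| 2 | 12.71 | 0.45 to 31.9 |
| 3 | 4.30 | 0.52 to 6.28 |
| 8 | 2.36 | 0.66 to 2.04 |
| 10 | 2.26 | 0.69 to 1.83 |

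**4. Effect on intervals.** Univariate random-effects pooling on the logit scale was simulated with study sizes from Table 1, 20,000 runs per setting. Assumptions: true value 85%, between-study SD 0.3 or 0.5 logit. For k = 3 the sizes are 947, 537 and 299.

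| Studies | Wald 95% coverage, SD 0.3 / 0.5 | SD estimated as zero, SD 0.3 / 0.5 |
|---|---|---|
| 2 | 76% / 73% | 26% / 17% |
| 3 | 83% / 81% | 14% / 6% |
| 8 | 87% / 87% | 3% / 0.2% |
| 10 | 89% / 89% | 0.6% / 0.05% |

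A small-sample t-based interval keeps about 95% coverage with two studies, at a price. At SD 0.5 its median half-width is 3.08 logits. Around logit(0.85) = 1.73 this runs from −1.35 to 4.81, which is about 21% to 99%. At three studies the half-width is 1.06 logits: 0.67 to 2.80, about 66% to 94%.

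**5. Do the planned sensitivity analyses help?** The balanced-trial analysis trims any trial above twice the median contribution. On full Table 1 counts the median is (271 + 293)/2 = 282, so the ceiling is 564. That cuts RIGHT-2 from 1149 to 564, about half, and RIGHT-2 has the clearest within-study mix. Neither this analysis nor the one with 26% mimics can give a single-status study the status it lacks.

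**The case against.** The strongest reply is that nothing breaks. In a patient-level model, LINCHPIN and RESTART simply add nothing to the haemorrhage specificity likelihood, and pooled values come from the remaining studies. That stands: a reader might infer that the estimates cannot be obtained at all, and the document does not support this.

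Several further limits also stand.
- The SAP names no bivariate model and no sensitivity–specificity correlation. A reader might add that this correlation is not identified. That would be true if no study held both statuses, but it faults a model the SAP does not specify. Separate fits are compatible with its wording.
- Primary outcome 2 does not rest on this model alone. Standard accuracy measures with Wilson intervals are also planned, although these ignore clustering.
- Two studies is the worst case. Table 1 types whole studies, not patients, and RIGHT-2 or bleeds in other trials may raise the number.
- If the ischaemia target means visible features, patients without them in the ischaemic trials are negatives, and ischaemia specificity could draw on up to eight studies. The wording of the outcome favours cause, and the wording of the target allows features.
- It is tempting to say that scanner or era differences would pass for detection of haemorrhage. The SAP gives neither by study, so that is conjecture.

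It may also be said that the ten studies are only the data source. Even so, the sentence promises to assess variation between them for every accuracy test, and for these two targets it cannot do so.

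**Conclusion.** The point holds in a limited form. For haemorrhage and ischaemia under primary outcome 2, the promised assessment across ten studies is not deliverable as worded. The haemorrhage part follows from Table 1 under any reading of the targets: at most eight studies inform specificity, and sensitivity comes mainly from two. The ischaemia specificity part is conditional on a cause-based reference. Ischaemia sensitivity has at most eight studies either way.

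On the sparse side the size depends on a count the SAP does not give. With two informative studies the multipliers are 12.7 for the mean and about 32 for the upper SD limit. With three they are 4.3 and 6.3. Simulated Wald coverage is 73% to 83% over these cases, under the assumed true value and SDs. Pooled point values remain computable. The problem lies in the between-study claim, the intervals, and the fact that the two measures come largely from different studies.

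The point does not extend to the ASPECTS cut-points in the ischaemic studies, and no claim is made about e-CTA.

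**What to change.** For ischaemia and haemorrhage under primary outcome 2:

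- Fit separate univariate random-effects models for sensitivity and specificity, each using only studies that have patients of the relevant status.
- State whether the ischaemia reference is cause or visible features.
- Report, for each estimate, the number of contributing studies and their patient counts.
- Where only a few studies contribute, use a small-sample interval and make no between-study variance claim. Set that minimum number before un-blinding; the SAP offers no basis for a particular value.
- Pre-specify a within-RIGHT-2 estimate of both measures, counts permitting, as a check on the contrast between cohorts, since that trial recruited at first ambulance contact.
- Limit the between-study wording to the studies that contribute to each estimate.

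The cost is some SAP wording and a simpler model. Heterogeneity will not be claimed for some estimates, and some intervals will be wider, markedly so if only two studies contribute.

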
### Primary outcomes

For these evaluations of e-ASPECTS, we will use a representative RITeS sample of NECT.

In two analyses, we will compare e-ASPECTS results to those provided by expert human readers for the assessment of non-enhanced brain CT acquired at baseline among patients presenting acutely with symptoms of stroke.

**
*Representative sampling for e-ASPECTS testing of primary outcomes.*
** Where clinical or demographic features are different to the comparator SSNAP/STTC/HERMES datasets (i.e. RITeS values should be within the range provided by the other datasets), we will use stratified random sampling to remove select cases (which are over-representing these features) to reduce these differences while maintaining the maximum sample size from the data available to RITeS. For example, if RITeS has 42% female patients and a median NIHSS of 19, we would identify all male patients with a high NIHSS and randomly remove subsets of these until the sex ratio and NIHSS are within the desired ranges. We will not select cases on the basis of the radiological features in Table 3.

To assess the impact of factors beyond our control which might affect the representativeness of our sample, we will perform sensitivity analyses of our primary outcomes for the following randomly selected subgroups: 1. With balanced representation from all RITeS trials, i.e. we will exclude surplus cases for trials which are relatively over-represented (more than double the median trial contribution).2. Where non-stroke mimics represent 26% of the total sample.

**
*1. Difference in ASPECT scores of e-ASPECTS and expert human readers.*
** We will compare e-ASPECTS and expert human results using overlapping histograms and Mann-Whitney U testing to assess the distribution of results, and Wilcoxon signed rank testing and Bland-Altman plots to assess pairwise agreement for each case. For results to be considered equivalent on Bland-Altman testing, we expect the range of agreement to be within ± 2 ASPECTS points. This is an arbitrarily derived but clinically meaningful difference that might lead to alterations in treatment for individual patients based on the thresholds presented below. We will also use K-alpha statistics to assess software-human reader agreement for these scalar data.

We will classify e-ASPECTS and expert-human scores into three groups to assess diagnostic accuracy at the following clinically relevant cut-points, and present a summary (receiver-operating characteristic) ROC curve: 1) ASPECTS 10 (normal) versus ASPECTS 0-9 (abnormal)2) ASPECTS 0-7 versus 8-10^2^.3) ASPECTS 0-5 versus ASPECTS 6-10^4^.

To compare with previous work, we will use Matthews correlation coefficient (MCC), and test non-inferiority between e-ASPECTS and expert-human scores^5^,^35^. We will calculate MCC as (TPxTN)-(FPxFN)/√(TP+FP)(TP+FN)(TN+FP)(TN+FN)^46^. We will set our non-inferiority margin at 5%. Thus using the two one-sided test (TOST) procedure, we will establish non-inferiority, using the following formula: at the α=5% significance level, if the lower limit of a (1-2α) × 100% (i.e. 90%) confidence interval for the difference (e-ASPECTS minus expert-human results) is above -5%. The confidence interval is set at (1-2α) rather than the usual (1-α) because the method is equivalent to performing two one-sided tests^47^,^48^.

**
*2. Accuracy of e-ASPECTS versus expert human readers for identifying cause of stroke symptoms.*
** We will compare the diagnostic accuracy of e-ASPECTS software and expert human readers (at baseline, blind to all other clinical data including further imaging) for three groups against the reference standard, human-expert opinion using all available follow-up data including further imaging: 1) Identifying features of ischaemic stroke (including ischaemic lesions in any brain location and/or intracranial hyperattenuating arteries)2) Identifying haemorrhage, and3) Identifying any structural causes of stroke symptoms on baseline imaging (including mimics).

In addition, to aid clinical understanding and real-world applicability, we will summarise all primary outcome results using normalised frequencies. Thus we will present results as proportions of 1000 individual patients, i.e. a test sensitivity of 90% would be presented as: the test will detect disease in 900 of 1000 patients with the disease, but 100 patients with the disease will be missed by the test^49^.

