To derive a ‘real-world’ dataset from all patients available to RITeS, and simultaneously maximise sample size, we will therefore: 1) Include all structural stroke mimics for e-ASPECTS testing (since this will be far less than 26%, but see planned sensitivity analyses for our primary outcomes below)2)For the remainder of included patients (i.e. non-mimics), aim for sex and age mix, stroke severity and time since symptom onset similar to SSNAP, pooled thrombolysis/ thrombectomy RCT data, and haemorrhagic stroke registry data.3)Not exclude imaging based on quality.

The most recent SSNAP annual dataset (Apr 2018-Mar 2019) identified 87,635 patients presenting acutely with stroke and had 93% data completion. Of these patients, 47.8% were female, median age was 77 years, 87.1% of strokes were ischaemic, 12.4% were haemorrhagic (0.4% unknown), and the median NIHSS was 5. For 69.4% of patients, the time of symptom onset was known and the median time from stroke onset to baseline scan in these patients was 4 hours and 2 minutes^30^. A pooled analysis of nine thrombolysis RCTs by the Stroke Thrombolysis Trialists’ Collaborative (STTC) group included 6,756 patients of whom 45% were female, the mean age was 71 years, the mean NIHSS was 12, and the mean treatment delay was 4 hours^25^. A pooled analysis of seven thrombectomy RCTs by the Highly Effective Reperfusion evaluated in Multiple Endovascular Stroke Trials (HERMES) collaboration included 1764 patients of whom 47% were female, the median age was 67 years, the median NIHSS was 17, and the mean time from onset to randomisation was 3 hours^4^. A comprehensive, community-based audit of haemorrhagic stroke in Scotland (The Lothian Audit of the Treatment of Cerebral Haemorrhage, LATCH) included 137 patients with primary haemorrhagic stroke of whom 55% were female, the median age was 79 years, and the median Glasgow Coma Scale at presentation was 13^31^,^32^.

To ascertain the representativeness of the non-mimic cases within the RITeS dataset, we will report demographic and clinical data as per SSNAP, STTC, HERMES and LATCH data (see Table 2). We will report absolute differences, 95% confidence intervals and p-values for comparisons. We will also present continuous data components using overlapping histograms.

To ascertain the representativeness of relevant radiological features in RITeS, we will also report the features listed in Table 3.

**
*Sample for e-CTA evaluation.*

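### The rule that trims the primary sample bounds onset-to-scan time with a randomisation time, and its wide NIHSS range is not backed by a re-analysis of the primary outcomes at routine-care severity

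*SAP article*

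**What the plan says.** In the SAP article, the subsection on representative sampling for the primary outcomes compares RITeS with SSNAP, STTC and HERMES and states that "RITeS values should be within the range provided by the other datasets". Where a feature falls outside, over-represented cases are removed at random, "while maintaining the maximum sample size from the data available to RITeS". The worked example of a sample that needs trimming begins "if RITeS has 42% female patients and a median NIHSS of 19". Two sensitivity analyses of the primary outcomes follow: one balances the contributions of the source trials, the other sets the mimic share at 26%.

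The comparator times are defined under Inclusion and exclusion criteria:

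- SSNAP, among the 69.4% with known onset: "the median time from stroke onset to baseline scan in these patients was 4 hours and 2 minutes".
- STTC: "the mean treatment delay was 4 hours".
- HERMES: "the mean time from onset to randomisation was 3 hours".

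Table 2 places all three in one row, labelled "Time from stroke onset, hours", without saying where each interval ends. Tables 4 and 5 define the RITeS variable as onset to scan.

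On severity, the same section warns that pooled trial data "may include patients with more severe stroke than those seen in routine practice". It also says that SSNAP contains many patients who would not be candidates for reperfusion treatment.

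**The concern.** The range rule decides which scans enter the analysis of both primary outcomes, so each bound should measure the same quantity as the RITeS value held against it.

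For time, it does not. The lower bound is an onset-to-randomisation figure. Thrombectomy candidates are imaged to establish eligibility, so their scan comes before randomisation and their onset-to-scan time is shorter than 3 h. A RITeS sample timed like the HERMES patients could then be judged to contain too many early scans and lose some of them, purely because the clocks differ.

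For severity, the bounds are comparable in kind but far apart, and the upper one comes from a thrombectomy trial pool. Because trimming keeps the sample as large as possible, a severe starting sample would be cut back only to the edge of the range. It would then count as representative, and neither sensitivity analysis would show what the primary results look like at the severity of routine care.

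**Working it through.** **1. How the rule works.** Central values from the text and Table 2:

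| Feature | SSNAP | STTC | HERMES | Range |
|---|---|---|---|---|
| Female | 47.8% | 45% | 47% | 45 to 47.8% |
| Age, years | 77 | 71 | 67 | 67 to 77 |
| NIHSS | 5 (median) | 12 (mean) | 17 (median) | 5 to 17 |
| Time, h | 4.03 | 4 | 3 | 3 to 4.03 |

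The plan's example is reproduced: 42% female lies below 45%, and NIHSS 19 lies above 17. The example also settles the reading. A value of 19 is inside the HERMES interquartile range of 13 to 21, so the range must be that of the central values. The ranges also mix means with medians. The HERMES time is called a mean in the text but is printed as 3 (2-4) in Table 2, which is the format for a median and quartiles.

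**2. The time bound.** The window is 4.03 − 3 = 1.03 h wide. Its floor is a randomisation time; its ceiling is a true scan time. The lag from scan to randomisation is not in the document, so a range is assumed. Take the HERMES time as normal with centre 3 h and quartiles 2 and 4 h. The SD is then 1/0.6745 = 1.483 h. For a lag L, the scan-time centre is 3 − L and the share scanned before 3 h is p = Φ(L/1.483). To raise the median to 3 h by removing only scans before 3 h, a share d of the sample must go, where (p − d)/(1 − d) = 0.5, so d = 2p − 1.

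| Assumed lag, h | Scan-time centre, h | p | d |
|---|---|---|---|
| 0.25 | 2.75 | 0.567 | 13% |
| 0.50 | 2.50 | 0.632 | 26% |
| 0.75 | 2.25 | 0.694 | 39% |
| 1.00 | 2.00 | 0.750 | 50% |

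These shares describe a hypothetical sample with HERMES timing. They are not a forecast for RITeS.

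**3. The severity bound.** SSNAP NIHSS is 5 (2-11). A RITeS median of 17 would pass. It is 17 − 5 = 12 points above the SSNAP median and 17 − 11 = 6 points above its upper quartile. About three quarters of SSNAP patients score 11 or less, while at least half of such a RITeS sample would score 17 or more. If log(NIHSS + 1) is taken as normal, which fits the quartiles 2, 5 and 11 because 3, 6 and 12 are equally spaced on a log scale, about 14% of SSNAP patients score above 17.

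**4. What the other planned analyses cover.** Under the first secondary outcome, an ordinal regression of the absolute ASPECTS difference includes the Table 5 variables, among them NIHSS and onset-to-scan time. It uses the entire RITeS sample and is repeated in the representative sample. Diagnostic accuracy by subgroup follows only for variables significantly associated with a poorer result. This can show that severity or time matters for ASPECTS agreement. It does not re-estimate either primary outcome at SSNAP severity, and its dependent variable does not address the second primary outcome, the cause of symptoms.

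**The case against.** The strongest reply is that several comparators were chosen on purpose. The target is the population in whom the software would be used, not all stroke. The plan says that no precise case-mix data exist for that population, that trial pools may be too severe, and that SSNAP includes many patients outside the treatment decision. Bracketing between them is reasoned. This stands: the NIHSS range is not an error and should stay for the main sample. It gives no reason for combining different time intervals.

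Second, a shift in severity or timing would not be hidden. Table 2 reports differences from each dataset with confidence intervals, histograms are planned, and the regression uses the untrimmed sample. This also stands, so it would be wrong to say that the plan cannot reveal a shift. What remains uncovered is the effect of the shift on the primary estimates.

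Third, Table 2 does not define the RITeS interval, and the scan does not precede randomisation in every source trial: RIGHT-2 recruited at first ambulance contact. That is fair. Reading RITeS time as onset to scan rests on Tables 4 and 5. The three comparators differ from one another under any reading.

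Fourth, a reader might infer that losing early scans and accepting severe ones would inflate accuracy. The document does not support this. It treats the covariates that alter accuracy as not yet known, and early or mild scans that software and expert both score 10 agree perfectly, so removing them could worsen agreement.

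**Conclusion.** The point holds in two limited parts.

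- **Time.** The 3 h lower bound belongs to a different clock from the RITeS scan time it would be held against. Followed as written, the rule can remove early scans wrongly. Under assumed lags of 0.25 to 1 h, the floor is too late by that amount, in a window about 1 h wide. A reader might infer that early scans will in fact be lost; RITeS times are not given, so only the possibility is shown. The 13 to 50% figures also depend on the normal shape and on HERMES-like timing.
- **Severity.** The rule accepts a median up to 17 against an SSNAP upper quartile of 11. This follows from a deliberate range. The gap is that neither sensitivity analysis re-estimates the primary outcomes at routine-care severity, and the secondary regression covers this only in part. RITeS NIHSS values are not given, so the actual gap may be small.

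The rule defines the sample for both primary outcomes and the correction is cheap, so the change should be made before unblinding.

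**What to change.** 1. **Time.** In Table 2, state the interval for each dataset: onset to scan, to treatment, or to randomisation. Report the STTC and HERMES times for description only and remove no case because of them. Judge RITeS onset-to-scan time against SSNAP onset to scan alone, with a stated tolerance, for example a RITeS median within the SSNAP interquartile range of 2 to 11 h. The single SSNAP median of 4 h 2 min should not be the target, because any median below it would then fail and more early scans would go than under the present 3 h floor.

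2. **Severity.** Keep the NIHSS range for the main sample. Add a third sensitivity analysis of both primary outcomes in a random draw matched to the SSNAP NIHSS distribution (median 5, quartiles 2 and 11), among non-mimic cases with NIHSS recorded. Note that the SSNAP figures cover all strokes, about 87% of them ischaemic, whereas the plan describes the Glasgow Coma Scale as the severity measure for haemorrhagic stroke. State how cases without NIHSS are handled in this analysis.

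The cost is a table footnote, one revised criterion and one more random draw. The matched subsample will be smaller than the main sample, so its intervals will be wider.
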